#### Trial closure

The end of the trial is defined as 12 months following the last follow-up visit of the last patient randomised, to allow for data entry and data cleaning activities to be completed.

### Sample size

Fifty-seven participants who are eligible and have provided informed consent will be recruited and randomised on a 2:1 ratio, with 38 allocated to receive the intervention and 19 to receive placebo. This sample size will aim to detect a difference of 20 mm^3^ in OBV with 90% power based on a 2:1 allocation ratio, and based on a standard deviation of 20 mm^3^ [69] with an assumed 10% drop-out rate accounting for the above MRI-based exclusions.

### Recruitment

Recruitment will take place over 12 months. Patients will be identified through the Smell & Taste Clinic at the James Paget University Hospital as well as from members of Fifth Sense who will be alerted via membership channels including social media and mailshots to contact the study team. Those identified from either source will be sent the relevant patient information pack (by mail/e-mail/website download). The CI and RN will screen potential participants to check their eligibility Those who contact the team via Fifth Sense will be asked to seek a GP referral to the Smell & Taste Clinic to enable recruitment. Depending on COVID-19-related restrictions at the time of commencing the study, the initial screening may be undertaken via telephone with the final eligibility checks undertaken at the baseline study visit at the UEA Brain Imaging Centre (UBIC) when they undergo their first MRI scan. In this latter scenario, the baseline Sniffin’ Sticks test will also be performed at this visit by the research associate. All necessary precautions for COVID-19 screening will be undertaken and national and local policies will be adhered to for any face-to-face contact, depending on the measures in place at the time of study commencement. Enrolment and informed consent will be undertaken by the CI and confirmed by the RA at UBIC.

### Assignment of interventions

#### Sequence generation

Participants will be randomly assigned to either the intervention or the placebo group with a 2:1 allocation as per a computer-generated randomisation schedule. The randomisation will be performed after the initial baseline MRI scan to ensure the eligibility criteria are fully met.

#### Allocation concealment mechanism and implementation

The random allocation order will be generated before the trial begins and concealed from the research team by a CTU statistician. An interactive web randomisation system (REDCap) will be used to generate a “pack ID” for the dispensing IMP for the allocation of participants to one of the two groups after the informed consent and baseline measures have been completed. The method of using pack identification numbers ensures the blind is maintained and medication can be dispensed by blinded members of the team. The patient will be allocated a participant number at the time of consent. When the results of the baseline tests, and all other pre-designated questions are completed in the CRF, the allocated staff will then have access to the randomisation process for that participant. The pack ID will be revealed and linked to that participant number.

#### Blinding (masking)

All participants, care providers, and outcome assessors will be blinded to the treatment allocation. Accidental unblinding will be logged and monitored to ensure that appropriate steps are taken to prevent this from reoccurring. The data analysts will not be blinded as they are required to know the group for the preparation of the DMEC reports.

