#### Statistical analysis plan

A full SAP will be produced prior to the analysis of any data. The SSC will be given the opportunity to comment on the SAP prior to it being signed-off by the CI and lead statistician.

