#### Data monitoring oversight

The trial will be led by the chief investigator working with the co-applicants who provide expertise in statistics, methodology, data management, functional imaging, and computational modelling. A research associate (RA) will be employed to undertake the day-to-day running of the study. Study activities and responsibilities will be documented in an overarching trial management agreement and signed by the James Paget University Hospital, CI, and the Clinical Research Network. The RA will maintain essential documentation with a study Master File and the CI will manage the regulatory and ethics approval process.

The Project Management Group (CI, RA, research nurse, other co-applicants as needed) research team will meet regularly (monthly during the setup phase then 2 monthly during the recruitment phase) to draft, review, and approve key essential documents including any documentation needed for research governance. The study steering committee will meet twice a year and include all co-applicants and affiliated research team members including our PPI representative. Online meeting platforms will be used where needed. Ad hoc meetings will be added where needed for any issues arising including safety monitoring. The Independent Steering Committee will encompass the role of a safety committee for the purposes of this trial.

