#### Adverse event reporting and monitoring

Definitions of harm of the EU Directive 2001/20/EC Article 2 based on the principles of ICH GCP apply to this trial. We will notify the REC and sponsor of any unexpected serious adverse reactions. We will adhere to the Health Research Authority guidelines [88].

All adverse events will be recorded in the database, to monitor for harm and allow for an ongoing comparison between arms for the data monitoring and safety committee in any subsequent RCT. All non-serious AEs and ARs, whether expected or not, should be recorded in the patient’s medical notes and reported in the database. Serious Adverse Events (SAEs) and Serious Adverse Reactions (SARs) must be notified to NCTU and the sponsor within 24 h. When an AE or AR occurs, the investigator responsible for the care of the participant must first assess whether the event is serious. If the event is classified as ‘serious’ then it will be reported in an expedited manner using the study-specific reporting form. The CI (or delegate) will assess whether the event could be related to trial treatment.

If there is at least a possible involvement of the trial intervention (including placebo), the CI must assess the expectedness of the event. An unexpected adverse reaction/event is one that is not reported in the approved version of the Reference safety Information (RSI) in the Vitadral SmPC, or one that is more frequently reported or more severe than previously reported. If a SAR is assessed as being unexpected it becomes a SUSAR (suspected, unexpected, serious adverse reaction) and REC reporting guidelines apply. If the sponsor and CI deem the event relevant, it will also be reported to the MHRA via their Yellow Card scheme.

The SSC in their role as Safety Committee will be provided with all safety data, along with the corresponding treatment arm, by the trial statistician. The committee can advise that the trial is stopped early in the unlikely event that there are concerns of harm to the participants.

We will withdraw any female participant who becomes pregnant. Female participants will be asked to inform the RA if they become pregnant during the course of the study.

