#### Study team

A research associate (RA) will be employed to undertake the day-to-day running of the study. A Senior Trial Manager (STM) at Norwich CTU will assist the CI and RA with study planning, study set-up prior to the appointment of the RA, oversight of study management, and adherence to CTU practices. The STM provides expertise in trial design, methodology, and conduct throughout the project. A Senior Statistician at Norwich CTU will provide advice throughout the study and statistical oversight and will be supported by a project statistician throughout the study.

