#### Independent study steering committee

The Independent Study Steering Committee (SSC) will include two experienced physicians independent of the trial and is the independent group responsible for oversight of the study in order to safeguard the interests of participants. The SSC provides advice to the CI, NCTU, the funder, and sponsor on all aspects of the trial. The membership, frequency of meetings, activity (including trial conduct and data review), and authority will be covered in the SSC terms of reference. Due to the nature of the trial proposed, the SSC will incorporate the role of a safety committee as defined below:To detect any trends, such as increases in un/expected events, and take appropriate actionTo seek additional advice or information from investigators where requiredTo evaluate the risk of the trial continuing and take appropriate action where necessary

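### The blinding section leaves the data analysts as a group unblinded for reports to a DMEC that the article does not set up; the only stated need is one statistician supplying safety data by arm to the SSC

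*Protocol article*

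**What the plan says.** The Blinding (masking) section first lists who is blind: "All participants, care providers, and outcome assessors will be blinded to the treatment allocation". It then makes one exception, with one reason: "The data analysts will not be blinded as they are required to know the group for the preparation of the DMEC reports".

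Elsewhere the safety role lies with the steering committee. Data monitoring oversight says: "The Independent Steering Committee will encompass the role of a safety committee for the purposes of this trial". The section on the independent study steering committee agrees: "Due to the nature of the trial proposed, the SSC will incorporate the role of a safety committee as defined below".

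Adverse event reporting and monitoring makes the trial statistician responsible for giving the SSC the safety data together with treatment arm. That section mentions a data monitoring body only for a later trial, where it speaks of an "ongoing comparison between arms for the data monitoring and safety committee in any subsequent RCT".

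On staffing, the Study team section describes a senior statistician at the clinical trials unit (CTU) who "will be supported by a project statistician throughout the study". On the SAP, the article requires a full plan before any data are analysed, and adds: "The SSC will be given the opportunity to comment on the SAP prior to it being signed-off by the CI and lead statistician".

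**The concern.** An exemption from blinding should reach no further than its reason. Here the reason is reporting to a committee that the article does not otherwise mention, and the exemption covers a class of people with no limit by person, dataset or time.

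The breadth matters because the article leaves judgement to whoever analyses the data. Under Statistical methods, OBV is compared by a two-sample t-test and then, in the same section, by a comparison adjusted for baseline. Additional analyses adds a general linear model, and non-parametric methods if assumptions fail. Seed regions and machine-learning pipelines follow for the imaging outcomes. An analyst who can link outcomes to allocation while such choices are open could be influenced by the result. Keeping the analyst blind until lock removes that route without relying on how much the SAP fixes in advance.

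The primary outcome is also a measurement taken from scans, and the article does not say where the line runs between outcome assessors, who are blind, and data analysts, who are not.

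**Working it through.** No figure in the plan is at issue, so the check is to set the sections side by side.

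1. **Is there a DMEC?** The term appears only in Blinding (masking). It is not in the abbreviations list, which has a DMC, expanded as a data management committee. Three sections (Data monitoring oversight, Adverse event reporting and monitoring, Independent study steering committee) give the safety role to the SSC. The one reference to a data monitoring and safety committee concerns a subsequent RCT. The committee figure in the appendix is not visible, but the text is consistent without it.

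2. **Is there a real need to unblind anyone?** Yes. By-arm safety data go to the SSC in this trial. Once the committee's name is corrected, the reason survives for the person who prepares them.

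3. **How many people does that need cover?** The adverse event section names one role, the trial statistician. The blinding section unblinds the analysts in the plural, without limit. The difference between the two is the excess.

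4. **Can the roles be separated with the staff described?** The Study team section gives a senior statistician and a project statistician, so two roles exist. Two points are open. The article does not say whether the lead statistician who signs the SAP is the senior statistician. Allocation concealment is assigned to a CTU statistician who is not further identified. The separation works only if the person who signs the SAP and runs the primary analysis does not hold the allocation list.

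5. **When is the SAP fixed relative to by-arm data?** It is to be produced before analysis of any data. Read plainly, that includes safety tables. Sign-off itself is tied to no milestone, and the article does not say in terms that a by-arm safety report counts as analysis. The SSC, which receives the by-arm safety data, may also comment on the SAP. One sentence would remove the doubt.

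6. **Would coded group labels be enough?** No. Allocation is 38 to 19, so group sizes reveal the arms. Restricting access is what protects the blind.

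**The case against.** The strongest reply is that this is a slip in a committee's name. By-arm reports are required, somebody must prepare them, and the trial statistician is named for the task; the plural in the blinding section is loose wording. Access rules often sit in the SAP, the monitoring plan or the SSC terms of reference, none of which is shown. In a mechanistic proof-of-concept study, an openly declared unblinded statistician is a legitimate choice.

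Much of this stands. The need to unblind one person is real, and the detail of access control may well be elsewhere. It does not remove the point, because the article does not leave the matter silent: it states a rule, and that rule is wider than its own reason.

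Three stronger readings are tempting, and the documents do not support them.

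- A reader might infer that the SAP is planned for signature after arm-level data have been seen. The requirement to produce it before analysis of any data is a real safeguard against that. The by-arm data described are safety data; nothing says that OBV is reported by arm during the trial.
- A reader might infer that those who process the scans are unblinded. The article does not say so. OBV is the primary outcome, so whoever measures it is more naturally a blinded outcome assessor.
- A reader might attach an inflated false-positive rate to the unblinding. Such a figure would measure freedom to choose among analyses, which is a matter of prespecification, and not the effect of an analyst knowing the allocation.

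**Conclusion.** The point holds in a limited form. The blinding section rests on a DMEC that the rest of the article replaces with the SSC, and it unblinds a group where the stated task needs one statistician. The boundary between outcome assessors and data analysts, and the order of SAP signature and first by-arm safety report, are unclear rather than wrong.

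The size cannot be put in numbers from the documents. No sample size, power or effect figure changes. It is a worthwhile correction because it replaces a stated rule with a less bias-prone one at little cost, in a trial meant to support a larger RCT.

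The conclusion assumes that the unseen committee figure does not show a separate DMEC. The remedy assumes that the statistician who signs the SAP and runs the primary analysis is not the CTU statistician who conceals the allocation.

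**What to change.** - **Blinding (masking):** replace the reference to DMEC reports with SSC safety reports. Limit unblinding to the one statistician who prepares the SSC safety tables, in line with the adverse event section.
- **Same section:** state that everyone who measures or processes images counts as a blinded outcome assessor. State that they, and the statistician who signs the SAP and runs the primary analysis, have no access to allocation until OBV measurement is complete and the database is locked. Confirm that this statistician does not hold the allocation list.
- **Statistical analysis plan:** state that the SAP is signed before the first by-arm safety report is issued. This makes clear that safety tables fall under the existing requirement.

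The cost is wording and database permissions. Two statistician roles are already described, so no extra staff should be needed if the assumption about the allocation list holds. The downside is that the lead statistician cannot cross-check the by-arm safety tables before lock.

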#### Emergency unblinding

Where possible, requests for emergency unblinding of individuals should be made via NCTU in agreement with the Chief Investigator, will be sought. However, in circumstances where there is insufficient time to make this request or for agreement to be sought, the treating clinician can make the decision to unblind immediately. This can be done via the study database. The Chief Investigator will have special logins which will allow unblinding of individual patients. This is closely audited within the database management system. All instances of unblinding should be recorded and reported to NCTU by the local principal investigator, including the identity of all recipients of the unblinding information.

### Data collection methods

#### Confidentiality

Each participant will be given a unique trial Participant IDentification number (PID). Data will be collected at the time-points indicated in the Trial Schedule. The preferred method of data collection is direct online entry of data onto the central database, stored on servers based at NCTU by members of the APOLLO trial team working within each research site. Data may be entered onto paper Case Report Forms (CRFs) prior to entry into the database. Staff will receive training on data collection and use of the online system.

Data collection, data entry, and queries raised by a member of the APOLLO trial team will be conducted in line with the NCTU and trial-specific Data Management Standard Operating Procedure. Identification logs, screening logs, and enrolment logs will be kept at the trial site in a locked cabinet within a secured room.

Clinical trial team members will receive trial protocol training. All data will be handled in accordance with the Data Protection Act 2018 and the General Data Protection Regulation (GDPR) (EU) 2016/679.

Participant identifiable data will be stored on a Participants Database to enable patients to be contacted by site staff for the purpose of contacting participants and sending questionnaires; and the central trial team for the purpose of sending newsletters during the trial. There will be a clear logical separation of participant-identifiable data from the trial data.

#### Data collection

Data will be entered under the participants’ PID number onto the central database stored on the servers based at NCTU. Study data are collected and managed using REDCap [74, 75] electronic data capture tools hosted at Norwich Clinical Trials Unit (NCTU). REDCap (Research Electronic Data Capture) is a secure, web-based software platform designed to support data capture for research studies, providing audit trails for tracking data manipulation and export procedures and automated export procedures for seamless data downloads to common statistical packages.

Access to the database will be via unique, individually assigned (i.e. not generic) usernames and passwords, and only be accessible to members of the APOLLO trial team at NCTU, and external regulators if requested. The servers are protected by firewalls and are patched and maintained according to best practices. The physical location of the servers is protected physically and environmentally in accordance with the University of East Anglia’s General Information Security Policy 3 (GISP3: Physical and environmental security).

#### Data management

The database and associated code will be developed by NCTU Data Management, in conjunction with the APOLLO trial team. The database software provides a number of features to help maintain data quality, including maintaining an audit trail, allowing custom validations on all data, allowing users to raise data query requests, and search facilities to identify validation failure/missing data.

After completion of the trial, the database will be retained on the servers of NCTU for on-going analysis of secondary outcomes.

The identification, screening, and enrolment logs, linking participant identifiable data to the pseudo-anonymised PID, will be held locally by the trial site. This will either be held in written form in a locked filing cabinet or electronically in a password-protected form on hospital computers. After completion of the trial, the identification, screening, and enrolment logs will be stored securely by the sites for 5 years unless otherwise advised by NCTU.

#### Non-adherence and non-retention

The consent form will explain that if a participant wishes to withdraw from the study the data and samples acquired prior to that point will be retained. Reason for withdrawal will be recorded, if given, as will loss to follow up.

Non-adherence to trial medication will be assessed by weighing the bottles for residual volume when returned to the RA at the 3-month visit; the pre-trial bottle weight will be recorded prior to dispensing. We will also collect blood samples to measure brain-derived neurotrophic factor (BDNF) as a proxy for a measure of the use of vitamin A. Blood samples will be taken by a research nurse at the Norfolk and Norwich University Hospital (NNUH) clinical research facility at both study visits using a S-Monovette 7.5 ml Z tube (with clotting activator) and left to coagulate for 30 min at room temperature and then centrifuged at 2000 × *g* for 10 min. The serum supernatant will then be placed into an ELISA (enzyme-linked immunosorbent assay) for BDNF. These samples will be stored at − 80 °C in a Biorepository until all the samples are collected. The assays will be undertaken at the end of the trial. Once the final outcomes are reported, the samples will be destroyed.

Where patients are unable or unwilling to continue to undertake study measurements/activities, the decision as to whether the participant should continue with trial treatment and/or follow-up assessments will be at the discretion of the CI.

### Statistical methods

#### Outcomes

The comparison between groups will be based on the intention-to-treat population. The OBV will be compared between the two groups using a two-sample *t*-test. The brain imaging data will be analysed in SPM12 (UCL, London, UK) [76], based on probabilistic maps of the region of interest derived from a meta-study [77], as well as anatomical markers [78, 79]. In order to address the primary outcome measure; changes in OBV, will be compared to the control group using a two-sample test of outcome measures adjusted for baseline. The second outcome measure of changes in orbitofrontal sulcus depth will also be analysed in the same manner. To understand the wider impact of anosmia on brain function we will use resting state fMRI analysis with novel brain network and machine learning pipelines [79]. In a similar approach to Lee et al. who investigated olfactory functional networks in Parkinson’s disease dementia and Alzheimer’s dementia [80, 81], we will use a regions of interest seed-based approach for the comparison of functional changes in the resting-state networks. The seed regions of interest we aim to investigate are the olfactory bulb, olfactory tract, piriform cortex, and orbitofrontal cortex (OFC) between groups. While OBV measurement has been widely used to investigate olfactory diseases, white matter integrity analyses are more recent. DTI analyses allow the evaluation of different fibre properties in white matter. Güllmar et al. showed that improvement of olfaction in chronic rhinosinusitis patients following surgery correlated with olfactory performance and DTI measures of cortical change [82]. In our study, the diffusion MRI analysis will be conducted with a reproducible, robust, and efficient dMRI processing pipeline [83]. We will also plan to use a diffusion tensor imaging sequence for the olfactory bulb and then use a white-matter skeleton co-registration approach (e.g. tract-based spatial statistics) to reduce inter-individual differences [84]. The use of advanced machine learning algorithms will allow us to go beyond simple correlations to make predictions and rank the effects of the intervention [84–86]. The ASL data will be analysed using an automated pipeline which includes optimised pre-processing with partial volume correction, vascular artifact reduction as well as extensive quality control and data provenance [87].

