**Methods/design:**

The study will compare 10,000 IU once daily Vitamin A self-administered intranasal drops versus peanut oil drops (placebo) delivered over 12 weeks in patients with post-viral olfactory loss. Potentially eligible patients will be recruited from the Smell & Taste Clinic and via the charity Fifth Sense. They will be invited to attend the Brain Imaging Centre at the University of East Anglia on two occasions, 3 months apart. If they meet the eligibility criteria, they will be consented to enter the study and randomised to receive vitamin A drops or no treatment in a 2:1 ratio. MRI scanning will enable volumetric measurement of the OB and ROS; fMRI will then be conducted using an olfactometer to deliver pulsed odours—phenethylalcohol (rose-like) and hydrogen sulphide (rotten eggs). Participants will also perform a standard smell test at both visits as well as complete a quality-of-life questionnaire. Change in OB volume will be the primary outcome measure.

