### Outcomes

**Table Taba:** 

Primary	Primary outcome measure: Olfactory bulb volume (OBV) (on MRI scan)
Secondary	• Right orbital sulcus volume (MRI scan) • Blood-oxygen-level-dependant (BOLD)-signal in primary olfactory areas; amygdala, piriform, and insula (fMRI scan) • Cerebral blood flow (CBF) in primary olfactory areas; amygdala, piriform, and insula • Psychophysical smell test (TDI) score • Olfactory disorders questionnaire (ODQ) score • Brain-derived neurotrophic factor (BDNF) (pg/ml)

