#### Additional analyses

An adjusted analysis will also be conducted adjusting for the corresponding baseline measure using a general linear model. A similar analysis to the OBV and sulcus measurement analysis will be used for the TDI score from the Sniffin’ Sticks psychophysical smell test and the ODQ. If the assumptions of the tests are not met, then non-parametric approaches will be used. We will also assess the correlation between the OBV measurements and the TDI scores using Pearson’s correlation coefficient.

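### The primary OBV analysis is stated in two unreconciled ways, and the baseline-adjusted model that would serve best is left as an additional analysis

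*Protocol article*

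**What the plan says.** All references are to the protocol article.

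- **Statistical methods, Outcomes, first statement:** "The OBV will be compared between the two groups using a two-sample" t-test. No baseline term is mentioned.
- **Same paragraph, second statement,** introduced as addressing the primary outcome measure: "changes in OBV, will be compared to the control group using a two-sample test of outcome measures adjusted for baseline".
- **Additional analyses:** "An adjusted analysis will also be conducted adjusting for the corresponding baseline measure using a general linear model".
- **How the outcome is named:** the abstract says "Change in OB volume will be the primary outcome measure"; the outcomes table says "Primary outcome measure: Olfactory bulb volume (OBV) (on MRI scan").
- **Sample size:** the trial aims to "detect a difference of 20 mm^3^ in OBV with 90% power", "based on a standard deviation of 20 mm^3" (mm³), with participants "recruited and randomised on a 2:1 ratio, with 38 allocated to receive the intervention and 19 to receive placebo" and an assumed 10% drop-out. The section does not say whether the SD is that of OBV at 12 weeks or of change in OBV.
- **Availability of baseline:** under Sequence generation, randomisation follows the baseline MRI. Under the exclusion criteria, a combined OBV above 85 mm³ rules a patient out. Everyone properly randomised therefore has a baseline OBV.

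**The concern.** The two statements in the Outcomes paragraph concern the same primary outcome and do not describe the same analysis. The first is an unadjusted comparison of OBV. The second is about change and claims adjustment for baseline, but names a two-sample test, which in the usual sense has no covariate. It can be read as a t-test on change scores or as an analysis of covariance. On the covariance reading, the same model is both primary and, under Additional analyses, an extra.

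Two things are at stake. First, the test that decides the trial is not fixed: 12-week OBV, change in OBV and baseline-adjusted OBV can give different p-values and interval widths on the same data. Second, the clearest reading of the lead statement leaves out a covariate that is already measured in everyone, in a trial of 57 people. Which analysis the stated power belongs to also depends on what the SD of 20 mm³ describes.

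**Working it through.** **Inputs from the document:** difference 20 mm³, SD 20 mm³, power 90%, allocation 2:1, total 57 (38 + 19), drop-out 10%.

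**Assumptions, because the document is silent:** two-sided 5% significance level; SD 20 taken as the SD of a single OBV measurement, equal at both visits; baseline-to-12-week correlation r of 0.3, 0.5 or 0.7.

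**Step 1. Reproduce the planned number.** Unadjusted two-sample t-test, noncentral t:

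- With 34 and 17 evaluable, the standard error is 20 × √(1/34 + 1/17) = 5.94 mm³.
- Noncentrality is 20 / 5.94 = 3.37 on 49 degrees of freedom. Power is 91.0%.
- This is the smallest 2:1 design that reaches 90%. Allowing for drop-out, 51 / 0.90 = 56.7, rounded up to 57.

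The planned 57 is reproduced exactly. A normal approximation gives 48 evaluable and 54 randomised; one-sided versions give 44 or 47. The sample size is therefore that of an unadjusted two-sided t-test whose outcome has an SD of 20 mm³.

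**Step 2. The candidate analyses at 34 + 17, difference 20 mm³.**

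- Change-score t-test: SD = 20 × √(2(1 − r)), 49 degrees of freedom.
- Linear model adjusted for baseline: residual SD = 20 × √(1 − r²), 48 degrees of freedom.

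| r | 12-week OBV t-test, power | Change SD (mm³) | Change-score t-test, power | Adjusted residual SD (mm³) | Adjusted model, power |
|---|---|---|---|---|---|
| 0.3 | 91.0% | 23.66 | 79.6% | 19.08 | 93.3% |
| 0.5 | 91.0% | 20.00 | 91.0% | 17.32 | 96.8% |
| 0.7 | 91.0% | 15.49 | 98.9% | 14.28 | 99.6% |

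**Step 3. Difference detectable with 90% power at 34 + 17.**

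| r | Unadjusted (mm³) | Adjusted (mm³) |
|---|---|---|
| 0.3 | 19.6 | 18.7 |
| 0.5 | 19.6 | 17.0 |
| 0.7 | 19.6 | 14.0 |

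**Step 4. What adjustment can lose.** At r = 0 the adjusted model has 90.96% power against 90.99% unadjusted, the price of one degree of freedom. The change-score test can lose much more: below r = 0.5 its SD exceeds 20 mm³ and it falls behind the plain t-test.

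**Step 5. If the SD of 20 mm³ is that of change.** The change-score t-test then has the 91.0% power of step 1. The other figures in steps 2 and 3 no longer follow, because the SD of a single measurement would be unknown.

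**The case against.** The strongest case for the plan has four parts.

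- **The text can be read as a coherent hierarchy.** A reader might infer three mutually incompatible primary analyses. The document does not support that. The general linear model is placed under Additional analyses and introduced as something done as well, so it sits comfortably beside an unadjusted primary test. It also fits a change-score primary, if adjustment for baseline is loose wording for change from baseline. The unresolved pair is in the Outcomes paragraph alone.
- **The abstract and the outcomes table do not contradict each other.** The table lists measured variables without a summary form for any of them. The abstract adds that the interest is in change. This stands, and the naming difference is not part of the finding.
- **The unadjusted t-test is legitimate.** It is valid under randomisation, its standard error already allows for chance baseline imbalance, and it gives the planned number exactly. A reader might also infer a distorted type I error from 2:1 allocation with unequal variances. The document gives no SDs by arm, does not say that the pooled form will be used, and provides a non-parametric fallback, so that inference is unsupported.
- **A full SAP is promised before any data are analysed,** with sign-off by the chief investigator and lead statistician. That limits the risk of choosing a test after seeing results. It does not remove two unreconciled statements from this document.

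The size of the gain is also uncertain. Excluding patients with OBV above 85 mm³ truncates the baseline distribution, which may lower the correlation and so the benefit of adjustment.

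**Conclusion.** The point holds in limited form. The Outcomes paragraph gives two unreconciled statements of the primary OBV analysis, the second of which is open to two readings. The baseline-adjusted model is left as an additional analysis although its covariate is available for everyone properly randomised.

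The consequence is an unfixed primary test and forgone precision. A reader might go further and infer a biased analysis or a wrong sample size; the document supports neither, and at its own target of 20 mm³ the unadjusted test is adequately powered.

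On the stated assumptions, adjustment lowers the detectable difference by about 1 mm³ at r = 0.3 (19.6 − 18.7 = 0.9) and by 5.6 mm³ at r = 0.7 (19.6 − 14.0). The choice between readings matters most at low correlation: at r = 0.3, power for 20 mm³ is 79.6% for a change-score test and 93.3% for the adjusted model. These figures rest on a two-sided 5% level, on SD 20 mm³ describing a single OBV measurement, and on assumed correlations.

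**What to change.** - Name one primary analysis: a general linear model of 12-week OBV on treatment arm and baseline OBV, reporting the adjusted mean difference with its 95% confidence interval.
- Keep the unadjusted t-test as a supportive analysis.
- Replace the sentence that combines a two-sample test with adjustment for baseline, and remove the same model from Additional analyses once it is primary.
- Use the same model for the sulcus measure, TDI score and ODQ score, each with its own baseline.
- In Sample size, state whether the SD of 20 mm³ refers to 12-week OBV or to change in OBV.

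The cost is wording in the protocol and SAP and one degree of freedom. No additional data or participants are needed.
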